### Statistical methods

7.13

Upon completion of the trial, all collected case data and questionnaire responses will be collated and summarized. Data storage will be managed using Microsoft Office 2017, while statistical analysis will be conducted using SPSS Statistics 27.0 software. Count data will be presented as the number of cases (N) and percentage (%). The distribution of continuous data will be assessed for normality; normally distributed data will be expressed as mean ± standard deviation, whereas non-normally distributed data will be presented as median (interquartile range) and quartile spacing (P25–P75). Baseline characteristics between the intervention and control groups will be compared using appropriate statistical tests, such as the independent samples t-test, Mann-Whitney U-test, and chi-square test, depending on the data type. Longitudinal analysis of follow-up data will be conducted using Generalized Estimating Equations (GEE) to compare differences in outcomes between the two groups. A two-sided test will be used, with statistical significance set at p < 0.05. In cases of missing data, multiple imputation techniques will be applied, given the random nature of the missing data. Multiple imputation involves generating multiple complete datasets by replacing missing values with plausible estimates derived from observed data and imputation models. This method preserves dataset variability and enhances result reliability compared to single imputation methods. Multiple imputation will be implemented using established statistical software like SPSS or R. Sensitivity analyses will also be conducted to assess the robustness of the results under various assumptions about missing data. This comprehensive approach ensures the validity and reliability of the study findings, accounting for missing data while maintaining statistical integrity throughout the analysis.

### Collection and archiving of data

7.14

During the trial, we will use the Questionnaire Star platform to collect survey data from all participants at baseline and during follow-up visits. These questionnaires can be accessed and completed online via a QR code, and they will collect information from participants, including sociodemographic and behavioral data. After the study concludes, the researchers will systematically organize and store all study-related data and documents, including exported questionnaires, group allocation records, follow-up information, laboratory test results, informed consent forms, and so on, into a database designated for this study. All raw data and documents will be archived in accordance with relevant laws and regulations after the trial ends.

### Investigator responsibilities

7.15

In this study, the primary responsibilities of the researchers include ensuring the scientific validity and rationality of the study design, protecting the rights of participants, ensuring the authenticity of data, and supervising the implementation of the study according to the research protocol. Prior to the commencement of the trial, researchers will train team members to ensure their familiarity with the study protocol and data collection procedures. During the study, regular supervision of team members’ fieldwork and documentation will be conducted.

Additionally, researchers will closely monitor and document any adverse events (AEs) experienced by participants during the intervention period, including psychological reactions, mood changes, behavioral alterations, and difficulties in using technology. Documentation will include the severity of the event, time of occurrence, duration, interventions taken, and final outcomes. Any serious adverse events (SAEs) identified will be reported in accordance with the regulations and timelines set by the Medical Ethics Committee of the Inner Mongolia Maternal and Child Health Hospital. For urgent SAEs, the study team will immediately implement necessary medical measures and promptly notify the ethics committee and sponsor.

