### Interventions

7.7

Compared with the control group, the intervention frequency is only once. That is, when distributing the HPV self-sampling kit, the intervention group needs to prepay to obtain the kit, while the control group can receive the HPV self-sampling kit without payment. Considering that the market price of an HPV self-sampling kit is around 20 RMB, we set the prepayment fee at 20 RMB. This can well simulate the real situation when the participants purchase the kit by themselves in daily life. Moreover, a proper deposit can avoid the problems caused by a high deposit: ① exceeding the participants’ affordability and thus reducing their willingness to participate; ② increasing the participants’ psychological pressure and causing unnecessary worries, which may affect the accuracy of the study results. On the other hand, a proper deposit can also avoid the problems caused by a low deposit: lack of effective constraints, leading to participants not taking the trial seriously and thus causing unstandardized sampling operations and other problems that may affect the trial results. We use the deposit as an incentive to encourage participants to actively provide feedback on the results of HPV self-sampling and to increase the feedback rate of HPV self-sampling results. The intervention flow chart is shown in **Figure 2**. To enhance participants’ psychological commitment and ensure active participation, the full prepayment amount will be refunded upon completion and feedback of the self-sampling results. Participants can choose from various convenient payment methods, including cash, bank transfer, or third-party payment platforms, to minimize payment costs and barriers. After self-sampling, participants in the intervention group can return the sampling kit to the corresponding Maternal and Child Health Care and Family Planning Service Center, which will then forward it to the Genetic and Eugenics Office of the Inner Mongolia Maternal and Child Health Care Hospital. A dedicated hotline will be established to facilitate timely feedback from participants. For those with positive HPV results, free follow-up medical services, including physician consultations and examination appointments, will be provided to ensure they receive proper treatment. Additionally, ongoing monitoring of participants’ adherence to treatment will be conducted.

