#### Primary outcome

7.11.1

The primary outcome of this study is the feedback rate of HPV-based self-sampling. It refers to the percentage of participants who mail back the tested HPV sampling kits to us within 1 month after receiving the HPV self-sampling kits, relative to the total number of HPV self-sampling kits distributed. If the feedback is not received within 1 month after distribution, it is considered as no feedback by default.

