##### HPV positivity rate and subsequent treatment adherence

7.11.2.1

The HPV positivity rate, defined as the proportion of participants testing positive for HPV through self-sampling, will be calculated based on laboratory-confirmed results using standardized PCR techniques. Data will be collected from certified laboratories, with a subset of samples retested for validation. Subsequent treatment adherence will be assessed by tracking participants’ attendance at recommended follow-up appointments and receipt of appropriate treatments following a positive HPV result. This will be monitored through electronic medical records and phone follow-ups at 1 and 3 months post-notification. Adherence will be recorded as a binary outcome and expressed as a percentage of participants who follow through with recommended care.

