### Follow-up

7.12

This is a six-month study and the intervention will be implemented during the first four weeks of subject enrollment. All subjects participating (both the “Pay-It-Forward” group and control group) are required to finish electronic questionnaires at two time points, including baseline and post intervention. The content of the follow-up visits varied across time points, with sociodemographic information and baseline health data collected only at baseline. Behavioral information, HPV self-sampling results, and participant satisfaction data will be collected at the 4-week post-intervention follow-up point. The specific follow-up and related data collection schedule is shown in **Table 1**.

**Table 1 T1:** Variables and measures collected at every time points.

Variables		Date source	Study Period	Baseline (T0)	Post-intervention (T1)
			timepoint	0w ± 1w	4w ± 1w
Intervention preparation	\	\	Informed consent	✓	\
	\	\	Random grouping	✓	\
	\	\	Online consulting service	✓	✓
Covariates	Individual	Baseline questionnaire	Sociodemographic information	✓	\
	Individual	Baseline questionnaire and Follow-up questionnaire	Behavioral information	✓	✓
Primary outcome	Feedback rate of HPV self-sampling	Laboratory records	Percentage of participants who return the HPV self-sampling kit within 1 month	\	✓
HPV infection status (Secondary Outcome)	HPV positivity rate	Laboratory records	Proportion of participants with lab-confirmed HPV-positive results (PCR testing)	\	✓
HPV self-sampling cognition and acceptance (Secondary Outcome)	HPV Self-Sampling Awareness	Follow-up questionnaire	HPV Self-Sampling Awareness Questionnaire	\	✓
	HPV self-sampling Satisfaction	Follow-up questionnaire	HPV self-sampling Satisfaction Questionnaire	\	✓
	HPV Self-Sampling Acceptance	Follow-up questionnaire	HPV Self-Sampling Acceptance Scale	\	✓
Cervical cancer health literacy and attitudes (Secondary Outcome)	Cervical Cancer-related Knowledge	Baseline questionnaire	Cervical Cancer-related Knowledge Scale	✓	\
	Cervical Cancer Screening and HPV Vaccination Attitude	Baseline questionnaire	Cervical Cancer Screening and HPV Vaccination Attitude Scale	✓	\
Psychology status (Secondary Outcomes)	depressed	Baseline questionnaire	PHQ-9	✓	\
	Anxiety	Baseline questionnaire	GAD-3	✓	\
	Stress	Baseline questionnaire	PSS-4	✓	\
	Family health	Baseline questionnaire	FHS-SF	✓	\
	Social support	Baseline questionnaire	PSSS-SF	✓	\
	personalities	Baseline questionnaire	BFI	✓	\

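### Adverse-event recording stops with the intervention period, about four weeks, so both planned calls to HPV-positive women and some late result notifications fall outside it

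*Protocol article*

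**What the plan says.** Section 7.15 (Investigator responsibilities) sets both the content and the period of adverse-event documentation: "researchers will closely monitor and document any adverse events (AEs) experienced by participants during the intervention period, including psychological reactions, mood changes". It gives no length in days.

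Two other sections bear on that length. Section 7.12 (Follow-up) states: "This is a six-month study and the intervention will be implemented during the first four weeks of subject enrollment". Section 7.7 (Interventions) says that "the intervention frequency is only once", meaning the prepayment when the kit is handed over.

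The result comes later in the sequence. Under 7.11.1 a kit counts as returned if it arrives "within 1 month after receiving the HPV self-sampling kits". Under 7.7, kits in the intervention arm go from the service centre to the hospital, and 7.11.2.1 has them tested by PCR. Section 7.10 promises prompt communication of results in the control arm, without a number of days. After a positive result, 7.11.2.1 plans "phone follow-ups at 1 and 3 months post-notification", described there as a way of tracking adherence.

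Table 1 has one later questionnaire visit, T1, at 4 weeks ± 1 week, labelled post-intervention. It shows PHQ-9, GAD-3 and PSS-4 at baseline only.

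**The concern.** The events that 7.15 names include psychological reactions and mood changes. One plausible occasion for them is hearing of a positive HPV result and going through the follow-up care. The plan keeps in touch with HPV-positive women for three months after they are told, but ties adverse-event documentation to a period that appears to end at about week four. Contact then continues after recording of non-serious events has stopped.

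At stake is how complete the record of non-serious harm is in the women most likely to go through follow-up. If the deposit raises returns as hypothesised, the intervention arm will also have more women with a positive result, so the gap would not fall equally on the two arms. The primary result is not affected.

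**Working it through.** The plan gives no figure to reproduce here; the question is one of timing.

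**Inputs from the protocol article**
- Recording window: the intervention period (7.15), read as days 0 to 28 from 7.12.
- Kit return on day u, with u from 0 to about 30 (7.11.1).
- Calls 1 and 3 months after notification (7.11.2.1), taken as 30 and 90 days.
- 54 women per arm, with return rates of 61.7% and 90% (7.5).
- HPV infection rate of 13.1% to 18.8% in the general population (section 1).

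**Assumed, because the article does not give it:** the turnaround L in days from kit return to notification, and the pattern of return times.

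**Step 1: the two calls.** Notification is on day u + L.
- 1-month call: u + L + 30 ≥ 30, which is later than 28.
- 3-month call: u + L + 90 ≥ 90, which is later than 28.

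This holds for every u and L. If the window is stretched to the outer edge of T1 (day 35), the 1-month call falls inside only when u + L ≤ 5 days, and the 3-month call never does.

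**Step 2: late notification.** A woman is told after day 28 whenever u + L > 28. A kit returned on day 30, within the permitted time, meets this even with L = 0. With returns spread evenly over 30 days, the share told by day 28 is (28 − L)/30. The other columns use assumed early, late and deadline-clustered patterns on the same 30 days.

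| Turnaround L | Early, Beta(1,2) | Even | Late, Beta(2,1) | At deadline, Beta(4,1) |
|---|---|---|---|---|
| 3 days | 97% | 83% | 69% | 48% |
| 7 days | 91% | 70% | 49% | 24% |
| 10 days | 84% | 60% | 36% | 13% |
| 14 days | 72% | 47% | 22% | 5% |
| 21 days | 41% | 23% | 5% | 0% |

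With even returns, more than half are told after day 28 only if (28 − L)/30 < 0.5, that is L > 13 days.

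**Step 3: number of women.**
- Kits returned: 54 × 0.617 + 54 × 0.90 = 33.3 + 48.6 = 81.9.
- Positive: 81.9 × 0.131 = 10.7 to 81.9 × 0.188 = 15.4, so about 11 to 15.
- By arm: intervention 48.6 × 0.131 = 6.4 to 48.6 × 0.188 = 9.1; control 33.3 × 0.131 = 4.4 to 33.3 × 0.188 = 6.3.

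**Step 4: does a longer window fit?** Recording to the 3-month call ends on day u + L + 90. With u = 30 and L = 3 to 14 (assumed), that is day 123 to 134, inside six months counted from a woman's enrolment.

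**The case against.** Several points on the other side are sound.

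- **A reader might infer that most positive results are told after the window closes.** The document does not support that. It gives neither a turnaround nor a return pattern, and with even returns and a turnaround of 10 days or less, at least 60% are told by day 28. Only *some* is supportable.
- **A reader might infer that no contact after a result falls inside the window.** T1, at day 21 to 35, can follow a result and lie inside or at the edge of it. Its post-intervention label argues against counting it as inside, but the claim is safe only for the two calls.
- **A reader might infer that serious events are lost too.** The sentence on serious events in 7.15 covers any that are identified and sets no time limit, and 7.16 has the data monitoring committee review safety data regularly. That inference fails, although the sentence does not say at which contact anyone asks.
- **The cause of distress is not stated.** No section names a positive result as the main trigger. Section 7.7 mentions pressure and worry from a high deposit, and the deposit is paid inside the window.
- **The period is not defined in 7.15.** Section 7.7 runs on to follow-up services and adherence monitoring, so a longer reading is conceivable. But 7.12 is the only section that gives the intervention a duration, and that is four weeks. The single-contact description in 7.7 would make the window shorter.
- **The article is condensed.** Adverse-event forms and schedules often sit in the full protocol, so the absence of an adverse-event row in Table 1 is not a finding. The limit on the period is different, because the article states it.

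**Conclusion.** The point holds in a limited form. If the intervention period in 7.15 means the four weeks in 7.12, both planned calls to HPV-positive women always fall after documentation of non-serious events has ended, and so does any notification after day 28. About 11 to 15 women are expected to be HPV-positive, assuming the planning return rates and that the cited general-population prevalence applies to the returned kits. For them, non-serious psychological reactions during follow-up care are not systematically recorded, and the same is true of reactions to a late result.

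How many are told late cannot be worked out from the document. Nor does it follow that distress would go largely unrecorded: reactions to the deposit and to early notification can fall inside the window. Safety is not among the objectives in 7.1, and acceptance and satisfaction are measured separately at T1, so no planned conclusion is overturned. This is a worthwhile, inexpensive improvement to safety capture; sample size and power do not change.

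**What to change.** In 7.15, replace the reference to the intervention period with a window running from kit distribution to the last planned contact. Define that contact as the 3-month post-notification call for HPV-positive women and, for all others, T1 or result notification, whichever is later. Ask the same brief adverse-event question in both arms at T1 and at the existing 1- and 3-month calls, so that capture does not differ by arm.

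This needs a wording change and one question on contacts already planned, with no new visit. The downside is somewhat more adverse-event reports to document.

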### Data monitoring

7.16

A Data Monitoring Committee (DMC) will be established for this study, comprising at least two members from the Medical Ethics Committee of the Inner Mongolia Maternal and Child Health Hospital. Operating independently of the study team, the DMC will regularly assess trial progress and safety data according to the established Data Monitoring Plan (DMP). The scope of monitoring will cover questionnaire data, monitoring results, and records of deposits and refunds. The primary responsibilities of the DMC are to ensure data integrity, evaluate participant safety, and protect participant rights. All monitoring activities will be conducted in a blinded manner to ensure data objectivity and the reliability of trial results. The DMC has the authority to immediately suspend or terminate the study if any non-compliance with the approved protocol or unauthorized changes in study procedures are detected. The Principal Investigator, Co-Investigators, and designated personnel from the Sponsor’s organization will have access to the final trial dataset. Additionally, external auditors, in addition to the Data Monitoring Committee, may also be granted access.

## Discussion

8

HPV-based self-sampling has emerged as a promising approach to increase cervical cancer screening coverage, especially in hard-to-reach populations (1). However, a critical challenge remains: the low feedback rate of self-sampling results, which undermines the effectiveness of screening programs (2). Enhancing the feedback rate of HPV self-sampling results is crucial for ensuring that women receive timely diagnosis and treatment, thus improving the overall efficacy of cervical cancer screening (3, 45). Pay-It-Forward interventions have shown potential in improving screening effectiveness by leveraging the psychological effect of commitment (4, 45). This study will explore the application of a Pay-It-Forward approach to increase the feedback rate of HPV self-sampling results, aiming to fill the gap in current screening strategies (1).

This study pioneers the application of the Pay-It-Forward method, a novel economic incentive approach, to improve the feedback rate of HPV self-sampling results. By requiring participants to pre-pay a certain fee, which is refunded upon completion of self-sampling and feedback of results, this model is expected to enhance participants’ motivation and sense of responsibility (46). This psychological commitment effect may lead to a higher feedback rate compared to traditional screening interventions (10, 47). Another innovation of this study lies in its extensive geographical representation and in-depth urban-rural disparity analysis. By covering all urban districts and surrounding counties of the city and equally recruiting participants from each region, we ensure the generalizability and fairness of the study results (15, 48). This design not only reduces selection bias but also promotes health equity by providing equal health intervention opportunities for women in different areas (16).

The Pay-It-Forward intervention is expected to be a feasible and innovative approach to improve screening participation and feedback rates. This approach may have a significant impact on cervical cancer screening-related public health policies by increasing the number of women who complete the screening process. The study also highlights the importance of addressing health inequalities by promoting more effective screening strategies that are accessible to women in ethnic minority regions. In the global effort to eliminate cervical cancer, this study seeks to contribute to international guidelines and strategies for HPV self-sampling screening. By providing evidence on the effectiveness of economic incentives in improving screening outcomes, it may inform the development of culturally-appropriate and effective screening programs worldwide.

A potential limitation of this study is the relatively small sample size, which may affect the statistical power and generalizability of the findings. Future research should consider larger sample sizes to validate the results and ensure broader applicability. Additionally, we acknowledge a potential selection bias in participant recruitment that may limit the generalizability of our findings to populations with lower health consciousness.

Future studies should explore different prepayment amounts and methods to determine the optimal approach for maximizing the feedback rate. Additionally, research on the cost-effectiveness of implementing Pay-It-Forward interventions in resource-limited settings is needed to inform practical applications. Based on the expected results, specific recommendations for culturally-adapted interventions and community engagement should be provided. These recommendations can guide the development of targeted screening programs that are sensitive to the needs and contexts of ethnic minority women. The potential application of similar economic incentive models to other health screening programs should also be discussed. This may include exploring how such models can be adapted to address other health issues and promote screening participation in diverse populations.

The findings of this study will highlight the potential of innovative economic incentives, such as the Pay-It-Forward approach, in enhancing the feedback rate of HPV self-sampling and improving overall screening effectiveness. These results will underscore the critical role of community engagement and culturally tailored interventions in addressing health disparities among ethnic minority populations. We advocate for the continued exploration of novel strategies in cervical cancer screening to ensure equitable access and improved health outcomes. Ultimately, this study supports the broader application of evidence-based interventions to drive meaningful progress in public health initiatives.

